#### Data analysis

Analyses will be undertaken on an intention-to-treat basis. The statistical analysis plan is for a primary comparison between intervention and control arms of the 12-month change in physical activity using an analysis of covariance model [66], with baseline values as the covariate to control for chance imbalances at baseline (accounting for any unequal variance due to the unequal allocation, and including the factors used in minimisation [67]). Analysis of interaction effects involving age-group or sex will be exploratory only and used to inform sample size planning for any subsequent definitive trial or evaluation. The analysis adopts a linear mixed model to provide the mean intervention effect together with quantification (as a standard deviation) of the individual participant differences in response to the intervention (‘treatment heterogeneity’) [68]. Confidence intervals, confidence levels, and magnitude-based inferences will be used to assess the clinical significance of the effect [64, 69, 70]. The same analysis strategy is applied to each dimension of physical activity, with due account taken of multiplicity [71]. In accordance with our second objective, for body weight and composition and metabolic control outcomes we will explore – using accepted regression-modelling methods – the extent to which intervention effects are mediated by changes in physical activity dimensions. Qualitative data will be analysed using thematic analysis based on constant comparison methods [72]. Techniques to enhance dependability and trustworthiness will include the development of a detailed coding scheme and coding checking protocol, cross-tabulation, negative case analysis and respondent validation (both in situ and by inviting feedback summaries of analysed data) [73].

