#### Randomisation/allocation

Eligible people will be randomised to one of two groups. We opt for an unequal allocation ratio (intervention: control) of 2:1, primarily to increase our experience with and amount of information on the new intervention [26] (the small loss of precision with unequal allocation only increases the total *N* required by 20). Participants will be allocated remotely by the trial statistician by concealed minimisation [27], providing balance across the trial arms for sex (male/female), age group (40–59 and 60–70 years), general practice, risk (medium/high) and PAL < 1.75 or ≥ 1.75. Although individual patients are the unit of randomisation, we believe that the threat of contamination within a practice is largely theoretical, especially given that the intervention is personalised.

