### Statistics

#### Number of participants

Although an exploratory trial, it is prudent and instructive to conduct a formal sample size estimation. For this purpose, our specific outcome is mean physical activity energy expenditure (expressed as PAL). In middle-aged men [4], the standard deviation for PAL was 0.18 (we have no reason to suspect a substantially different variability in women). Our targeted effect size is a difference between intervention and control arms in the 12-month change in PAL from baseline to follow-up of 0.07. Based on our previous data [4], an increase in PAL of that magnitude would result in an increase of 10 % in the proportion meeting the minimum physical activity recommendation of a PAL of 1.6 [63], which we define as the smallest worthwhile effect [64]. With 2*P* = 0.05, 90 % power, and an assumed correlation between baseline and follow-up values of *r* = 0.7, the required sample size with an Analysis of Covariance model [65] is 108 in the intervention and 54 in the control. Allowing for 25 % loss to follow-up (attrition) results in a final target sample size of 144 in the intervention group and 72 controls. The assumed correlation between baseline and follow-up (the 12-month reliability) is a conservative estimate, as we are aware of no long-term reliability data using the best objective measures. Note that we are not, a priori, attaching primacy to PAL and we will examine multiple physical activity dimensions. PAL permits a robust sample size estimate and is clearly important.

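### The exploratory age interaction is specified on a two-level age group although age in years is collected, which weakens an already imprecise estimate; modelling age in years is a cheap improvement

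*Protocol article*

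**What the plan says.** The Data analysis section gives one sentence to effect modification: "Analysis of interaction effects involving age-group or sex will be exploratory only and used to inform sample size planning for any subsequent definitive trial". The same section puts the minimisation factors into the covariance model for the primary 12-month comparison.

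The meaning of age group comes from Randomisation/allocation, where minimisation is described as "providing balance across the trial arms for sex (male/female), age group", with two age bands, 40–59 and 60–70 years, and further factors. Age in years is available: the Physical activity assessment section lists age among the inputs to the monitor's energy expenditure algorithm.

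The Number of participants section sizes the trial for the overall difference in PAL only. It calls the trial exploratory and gives no precision for any interaction.

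**The concern.** Cutting a continuous moderator in two treats a 40-year-old and a 59-year-old as alike, and a 59-year-old and a 60-year-old as different. If the treatment effect drifts with age, the two-group contrast estimates that drift less efficiently than a term in years would. The trial was sized for a main effect, so its interactions have little precision to spare.

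What is at stake is limited to the value of an exploratory result. The article gives that result a use, informing the planning of a later trial. A reader who took the observed interaction at face value for that purpose would be working with a very uncertain number.

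**Working it through.** **Inputs, all from the Number of participants and Randomisation/allocation sections**
- SD: "the standard deviation for PAL was 0.18"
- Correlation: "assumed correlation between baseline and follow-up values of *r* = 0.7"
- Target: "difference between intervention and control arms in the 12-month change in PAL from baseline to follow-up of 0.07"
- Error rates: "With 2*P* = 0.05, 90 % power"
- Allocation: "unequal allocation ratio (intervention: control) of 2:1"

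**Step 1. Reproduce the stated sample size.**
The residual SD after adjusting for baseline is 0.18 × √(1 − 0.7²) = 0.1285. At 2:1, the control arm needs 1.5 × [0.1285 × (1.960 + 1.282) / 0.07]² = 53.15, so 54, with 108 in the intervention arm. Dividing by 0.75 for attrition gives 72 and 144. At 1:1 the formula gives 71 per arm, 142 in all, so the stated cost of 20 for unequal allocation (162 − 142) also reproduces.

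**Step 2. Precision of the main effect.**
SE = 0.1285 × √(1/108 + 1/54) = 0.0214. The 95% half-width is 1.96 × 0.0214 = 0.042.

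**Step 3. Precision of a two-level interaction.**
If a share p of participants falls in one subgroup, with 2:1 allocation and the same residual SD in each subgroup, the SE is 0.0214 / √(p(1 − p)). The factor 1/√(p(1 − p)) is never below 2.

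| Split | Interaction SE | 95% half-width | Power for an interaction of 0.07 |
|---|---|---|---|
| 50:50 | 0.0428 | 0.084 | 37% |
| 67:33 | 0.0454 | 0.089 | 34% |
| 80:20 | 0.0536 | 0.105 | 26% |

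The splits are assumptions, since the article gives no age or sex distribution. With all 144 + 72 retained and a 50:50 split, the half-width is still 0.073.

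**Step 4. Information on age kept by the cut at 60.**
For a linear age effect, the share kept is the squared correlation between age and the indicator for 60 or over. For ages uniform on 40–70:
- the variance of age is 30²/12 = 75;
- the group means are 50 and 65, a difference of 15;
- the variance of the indicator is (1/3)(2/3) = 2/9;
- the share kept is 15² × (2/9) / 75 = 50/75 = 0.667, a loss of 33%.

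Other assumed age distributions, truncated to the eligible range:

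| Assumed ages | Loss |
|---|---|
| Uniform, counting 70-year-olds up to their 71st birthday | 31% |
| Normal, mean 62, SD 6 | 34% |
| Normal, mean 60, SD 7 | 34% |
| Normal, mean 58, SD 7 | 38% |
| Normal, mean 55, SD 7 | 46% |

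In terms of participants, keeping 0.667 of the information resembles estimating the age trend from 162 × 0.667 = 108 of the 162. Keeping 0.54 resembles 162 × 0.54 = 87.

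**The case against.** The strongest reply is that this is a secondary analysis in a trial the authors call exploratory. Imprecise interactions are expected there, the article labels them exploratory, and no confirmatory claim rests on them. That stands, and it keeps the point small.

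Four stronger readings are tempting, and the document does not support them.

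- **That the next trial will be sized on the observed interaction.** The article says only that these analyses will inform planning. Nothing says the point estimate will be entered into a formula. The authors' own sample size section works from a smallest worthwhile effect, which is the sounder approach.
- **That age group is the wrong covariate in the main model.** Adjusting for a minimisation factor in the form used for allocation matches the analysis to the design. The loss in step 4 concerns an age trend, and no loss has been shown for the treatment comparison.
- **That an interval wider than 0.07 in itself marks the interactions as weak.** The main effect's full 95% interval is 2 × 0.042 = 0.084 wide, in a trial with 90% power. The useful comparison is the half-width: 0.042 for the main effect, 0.084 or more for an interaction.
- **That a third of the age information is lost as a matter of fact.** The figure needs a linear effect and an age distribution that the article does not give. It would not apply to a step change at 60, and it says nothing about sex, which is binary in any case.

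It may also be said that moderator coding belongs in a fuller analysis plan that is not shown. Silence would indeed be no finding. Here, however, the article names age group as the moderator.

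**Conclusion.** The point holds as a cheap improvement. It is neither an error nor a contradiction. The exploratory age interaction is specified on two groups when age in years is at hand. Under a roughly linear age effect this gives up about 33% of the information on age for uniform ages, and about 46% if ages centre near 55.

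The loss falls on an estimate that is already imprecise: a two-level age or sex interaction in PAL has a 95% half-width of 0.084 to 0.105 against 0.07. That range rests on the article's SD, correlation and evaluable numbers, on equal residual variance across subgroups, and on assumed splits from 50:50 to 80:20. Using age in years would help the age interaction only; the sex interaction stays as imprecise as shown.

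The primary comparison is unaffected, and the stated 108 + 54 and 144 + 72 reproduce.

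**What to change.** In the Data analysis section:

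1. Keep age group as a minimisation factor in the main model, as planned.
2. Specify the exploratory treatment-by-age interaction with age in years, together with a simple check of linearity.
3. Report the age and sex interactions as estimates with confidence intervals.
4. State that any later sample size planning will use those intervals, or a smallest worthwhile interaction stated in advance, and not the observed point estimate.

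The change is to wording only. It needs no new data, no more participants and no change to randomisation. The small cost is the linearity check.

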Subsequent sessions will be approximately 20–30 minutes in duration. Prior to meetings, coaches will be encouraged to log-in to the platform and review participants’ profiles as a preparatory exercise to help inform session delivery. Once it is established that the participant is confidently self-monitoring and reviewing their data, the aim of the second session is to revisit the participants’ physical activity profile and to discuss aspects of their physical activity behaviour that they would consider changing. Here, there will be a particular emphasis on identifying opportunities for achievable but sufficiently meaningful modification and specific goal setting regarding what, where and how to act. Participants who have low activity in every dimension have the most ‘choice’ and will be guided through a menu of physical activity options. Participants who score well in one or more dimensions will be supported in adding to their existing behaviour knowing that what they are doing is recognised. In terms of the tone of advice provided, coaches will attempt to use neutral language and encourage choice (e.g. using terms such as ‘you may choose to’ or ‘how would you’ rather than ‘you should’ or ‘you must’) and show empathy (e.g. ‘I appreciate why you might find this difficult’). These vocalisations will be provided in a structured manner such that goals, strategies, and implementation intentions are clear, realistic, and well-defined [10].

The primary focus of subsequent sessions will involve reviewing the impact of any changes and in supporting all efforts the participant has made to be more active, as well as recalibrating specific goals and plans within the context of the individual’s existing behaviour and lifestyle. This process will be led by the participant and will inevitably be highly individualised. At the final session, participants will be encouraged to consider their progress by using the multidimensional profile to reflect on what has been achieved and to develop a future action plan towards long-term change.

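### The planned SD of individual response reflects only the difference in residual variance between arms, so it hides response that depends on baseline activity

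*Protocol article*

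**What the plan says.** The Data analysis section of the protocol article sets the primary comparison as the between-arm difference in 12-month change in physical activity, by ANCOVA with the baseline value as the covariate. It adds: "accounting for any unequal variance due to the unequal allocation, and including the factors used in minimisation". On interactions it says: "Analysis of interaction effects involving age-group or sex will be exploratory only". No baseline-by-arm term is mentioned. A linear mixed model is then to give the mean effect together with "quantification (as a standard deviation) of the individual participant differences in response to the intervention". The same strategy is applied to each dimension of physical activity.

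The intervention section describes coaching that starts from the participant's own profile: "Participants who have low activity in every dimension have the most ‘choice’ and will be guided through a menu of physical activity options". Participants who already score well in some dimension are helped to add to what they do.

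**The concern.** Each participant is in one arm and contributes one 12-month change, so nobody's individual response is observed. In the model as described, the only information on a response SD is how much more the intervention arm varies around the fitted line than the control arm does. That excess equals the variance of response under three conditions that the article does not state:

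- response is unrelated to baseline;
- response is unrelated to what the outcome would have been without the intervention;
- within-person variability is the same in both arms.

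The first condition is doubtful in this trial, because the intervention is built around the baseline profile. If the less active gain more, that is real and predictable heterogeneity, but a single baseline slope does not turn it into extra intervention-arm variance.

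The variance wording adds to the difficulty. It treats an arm difference in variance as a by-product of the 2:1 ratio. Two sentences later, the promised SD has to be drawn from that same difference. An allocation ratio changes how precisely each variance is estimated, not how large it is.

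At stake is a secondary result promised for every activity dimension. It could suggest little individual variation when response varies systematically with baseline, or suggest variation when only the week-to-week spread differs between arms.

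**Working it through.** **Inputs from Number of participants.** "With 2*P* = 0.05, 90 % power"; "the standard deviation for PAL was 0.18"; target difference in "12-month change in PAL from baseline to follow-up of 0.07"; "assumed correlation between baseline and follow-up values of *r* = 0.7"; 108 intervention and 54 control participants analysed.

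**The plan's own figure.** The ANCOVA residual variance is 0.18² × (1 - 0.7²) = 0.0324 × 0.51 = 0.01652, so the residual SD is 0.1285. At 2:1, control n = 1.5 × 0.01652 × (1.960 + 1.282)² / 0.07² = 53.15, rounded up to 54, with 108 in the intervention arm. Dividing by 0.75 for attrition gives 72 and 144. The stated numbers reproduce.

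**When the SD is right.** If response has SD 0.07 and is independent of baseline and of the untreated outcome, the excess variance is 0.07² = 0.0049, and a large-sample simulation recovers 0.070. Precision is low: the standard error of the variance difference at 108/54 is √(2 × 0.01652²/107 + 2 × 0.01652²/53) = 0.0039.

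**Response depends on baseline.** Let response be 0.07 + b × (centred baseline). Its true SD is |b| × 0.18. The article gives no value for b, so every slope here is an assumption. With one slope for both arms and equal weighting of participants, the fitted slope lies two thirds of the way towards the intervention arm's slope. The misfit added to the residual variance is (b/3)² × 0.0324 in the intervention arm and (2b/3)² × 0.0324 in control. The excess is therefore (1/9 - 4/9) × b² × 0.0324 = -b² × 0.0324/3, which is negative whichever sign b has.

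| b | True response SD | Expected excess variance | Estimate negative (simulated) | Interaction detected (simulated) |
|---|---|---|---|---|
| 0 | 0 | 0 | 50% | 5.5% (false positive) |
| -0.2 | 0.036 | -0.0004 | 52% | 40% |
| -0.3 | 0.054 | -0.0010 | 58% | 69% |
| -0.39 | 0.070 | -0.0016 | 64% | 90% |
| -0.5 | 0.090 | -0.0027 | 74% | 98% |
| -0.56 | 0.101 | -0.0034 | 79% | 99% |

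The simulations use 108/54, SD 0.18 and r = 0.7. The negative share should be read against the 50% that arises with no heterogeneity at all. At the milder slopes the estimate looks much as it would if everyone responded alike. At the steeper ones it moves further the wrong way as heterogeneity grows.

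The interaction column can be checked by hand. The slope's standard error is √[(0.01652/0.0324) × (1/108 + 1/54)] = 0.119. For b = -0.3 the ratio is 2.52, giving power of about Φ(2.52 - 1.96) = 71%, close to the simulated 69%.

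The PAL minimisation factor does not repair this. Adding a two-level baseline stratum as a main effect left the estimate negative in 79% of trials at b = -0.56.

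**Response depends on the untreated outcome.** With response SD 0.07 and correlation ρ with the untreated residual, the excess is 0.07² + 2ρ × 0.07 × 0.1285. It is zero at ρ = -0.07/(2 × 0.1285) = -0.27. Equal arm variances therefore do not imply equal response.

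**Within-person spread differs.** Take the within-person variance as 0.3 × 0.0324 = 0.00972. If the within-person SD is 25% larger in the intervention arm (an assumption) and response is identical for all, the excess is 0.00972 × (1.25² - 1) = 0.00547. This would be read as a response SD of 0.074, as large as the 0.07 target.

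**Mean effect.** It stayed at about 0.07 in every baseline-dependent and correlated-response scenario of the large-sample simulation.

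**The case against.** The article does not write out how the SD is extracted; it cites a reference. Excess variance and common slope are not its words, and random-effect structure is ordinary SAP detail. This limits the point but does not remove it. The article names the model, its covariates, the interactions considered and the interpretation of the SD. On that description the variance difference is the only source of the SD, and no assumption is attached to it.

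A reader might infer that the plan tests for heterogeneity and would draw a false conclusion about who benefits. The documents do not support that: they plan quantification with confidence intervals and magnitude-based inference, and a single SD could not identify who benefits.

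A reader might also infer that the response SD cannot be identified at all. That would follow only if an arm-specific residual variance and a separate random-response term were both fitted to the 12-month value alone. The article does not say that both are fitted. Activity is also measured at 3 months, and a mixed model using both follow-ups could separate them.

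The slopes are assumptions, and -0.56 is extreme. With a mean effect of 0.07 it implies a loss of 0.56 × 0.18 - 0.07 = 0.03 in PAL at one SD above mean baseline, and harm to about 24% of participants. That fits poorly with helping active participants add to their behaviour. The milder end of the range is the safer guide.

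Allowing for unequal variance is itself sound practice; only the stated cause is wrong. The caveat on within-person spread applies to any parallel-group trial without repeated treatment periods.

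**Conclusion.** The point holds in limited form. As described, the promised SD is an arm difference in residual spread, and it can be read as individual response only under the three unstated conditions. Tailoring to the baseline profile gives a specific reason to doubt the first of them. If that condition fails, the common slope at 2:1 drives the estimate below zero: it is negative in about 58% of trials at slope -0.3 and 79% at -0.56, against 50% with no heterogeneity. An interaction term finds the pattern in about 69% and 99%. These figures rest on assumed linear slopes, normal data and the plan's own SD, correlation and analysed numbers.

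Attributing unequal variance to the allocation ratio is an error on the face of the text. It would be wrong to infer that the primary comparison is biased or the trial undersized: the mean effect and the sample size are unaffected, and the trial describes itself as exploratory. The correction is still worth making, because the SD is promised for every dimension and the baseline data needed are already collected.

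**What to change.** In Data analysis:

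(a) For the heterogeneity analysis of each dimension, add a centred baseline-by-arm interaction. Report its slope with a CI beside the remaining, unexplained response SD. If a total SD is also reported, subtract the squared standard error of the slope from the squared slope before multiplying by the baseline variance. Without this, the variance is biased upward by about 0.119² × 0.0324 = 0.0005. The total variance can still come out negative and should then be reported as such. Keep the common-slope ANCOVA for the mean effect.

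(b) Delete the words that attribute unequal variance to the allocation, and simply allow arm-specific residual variances. If the model uses only the 12-month value, do not fit a separate random-response term as well.

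(c) Leave the variance difference unconstrained so that it may be negative, give its CI, and state the conditions under which it can be read as individual response.

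The cost is one degree of freedom in the heterogeneity model and a more guarded claim. No new data or participants are needed, and the mean-effect analysis does not change.

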## Discussion

It is important that physical activity fulfils its potential in making an effective contribution towards the success of public health initiatives. This paper describes the protocol for the Mi-PACT randomised controlled trial which aims to modulate physical activity, generate meaningful weight loss and improve metabolic health in patients at risk of cardiovascular disease and diabetes mellitus recruited from primary care. It is increasingly apparent that there are a variety of dimensions to physical activity that are independently important and we need to harness this information to avoid public confusion and disappointment regarding efforts to change physical activity behaviour. In particular, the marketing of informational feedback and set of physical activity options is potentially a key step in supporting increased engagement and sustained lifestyle modifications.

With technological innovation, the capture and provision of multidimensional physical activity ‘profiles’ is increasingly accurate, precise and scalable. In the present trial, we will examine whether multidimensional physical activity feedback from wearable physical activity monitors and self-monitoring using an online platform can be successfully incorporated into existing healthcare provision; and whether this leads to a meaningful change in physical activity in patients at risk of chronic disease. We envisage direct potential application within the context of public health initiatives (e.g. NHS Health Check). In addition, multidimensional physical activity profiling could become an adjunct to other public health strategies in primary practice (e.g. weight loss or cardiac rehabilitation).

